#### Blood tests

In routine clinical practice, blood samples are collected from patients prior to treatment initiation to assess parameters such as white blood cell count, liver and renal function and vitamin D levels. These assessments are repeated during regular follow up. In addition, serum levels of NfL and GFAP will be measured at screening, T1, T2 and T3. Circulating sICPs and lymphocyte subset distributions will be analysed in screening and T1.

#### Clinical tests

In addition to routine patient visits, at screening, T1, T2 and T3 the following clinical tests are conducted:

Extended Disability Status Scale (EDSS): EDSS is used to determine disability worsening and assess relapse related decline in neurological function.Timed 25-foot walking test (T25-FW): The T25-FW is a quantitative measure to assess mobility and lower leg limb function.9 Hole Peg Test (9HPT): The 9HPT is a manual dexterity performance measure and assesses disability in the form of upper limb function.

A questionnaire is administered at screening, T1, T2, T3 as well and considers urinary tract symptoms. They consist of a separate questionnaire for male (ICIQ-MLUTS) and female (ICIQ-FLUTS).

### Recruitment and eligibility criteria

We aim to include a population of treatment-naïve RRMS patients, 18–65 years old, early in the disease course, when a first DMT is initiated. Inclusion is performed in five Dutch MS centres; Zuyderland Medical Centre, Erasmus Medical Centre, Jeroen Bosch Hospital, Rijnstate Hospital and Albert Schweitzer hospital. In- and exclusion criteria have been explained in detail in Table 2.

**Table 2 Tab2:** In- and exclusion criteria

Inclusion Criteria	Exclusion Criteria
Diagnosed with RRMS (≤ 5 years since first clinical event)	First clinical event > 5 years ago
Age between 18–65 years	Age < 18 or > 65 years
Treatment-naïve patients starting a currently approved DMT in the Netherlands	Prior DMT initiation
	Incapable of giving informed consent
	Unable to undergo local MRI scan - Physical limitations (e.g., obesity, inability to lie flat) - Claustrophobia
	Contraindications for MRI scan - MRI-unsafe implants/devices (e.g., pacemaker, ocularmetal splinters) - Pregnancy at inclusion

Individual subjects will not be replaced after withdrawal. Sample size calculation has been done with correction for expected loss to follow up. This study does not include any interventions. Patients who choose to withdraw from the study will go back to receiving standard care.

### Statistics

#### Sample size

To estimate the incidence of asymptomatic cord lesions in absence of brain MRI activity, an approximate sample size of 139 will be needed, given an estimated proportion of asymptomatic cord lesions of 10% based on retrospective literature [6, 8, 20] (precision 0.05, confidence level 0.95).

CSF profiles are studied as a priori selected predictor and additionally we provide descriptive data and analyse associations in an exploratory fashion for the other different clinical, radiological, biochemical factors and treatments used in patients with/without new spinal cord lesions, to be able to identify important prognostic candidates, which in turn can be specifically studied in a possible future extension of the study.

Not all collected parameters are included in a prognostic model for spinal cord disease activity, because for the prognostic model to include a wide variety of predictors, a very large population is needed (estimated > 400), which currently is not feasible.

To assess a logistic regression model in which certain CSF profiles (primarily the degree of intrathecal IgM production) are associated with any new spinal cord lesion within two years of follow-up, an estimated sample size of 144 patients is needed to be able to detect an odds ratio of 2 (expected R-squared between main predictor variable and other covariates estimated 0.07 based on retrospective data) with a power of 80%, alpha of 0.05 given that the base expected proportion of patients with new cord lesions within two years is about 15%. The latter figure is based on retrospective data from a local database, where we found that 19% of patients (*n* = 217) developed new cord lesions (regardless of treatment) within 2 years of initiation of a new treatment [11]. In the international MSBase registry this figure was 12% for treatment-naïve RRMS patients starting a DMT (*n* = 528) [12].

Given the calculated sample sizes and an expected loss-to-follow-up of about 2–7% based on other longitudinal prospective MS MRI studies [9, 10], for this study we will aim to include 155 patients.

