**Fig. 2 Fig2:**
[figure not shown]
Overview of study timeline and collected data. See supplementary material for additional concise information

*At baseline*,* the following characteristics will be registered: age*,* sex*,* height and weight (body mass index)*,* comorbidities*,* cerebrospinal fluid data (if lumbar puncture took place as part of the diagnostic workup)*,* presenting syndrome*,* disease duration*,* family history of MS*,* previously performed cerebral and SC-MRI data.*

*Furthermore*,* MS related relapses*,* extra outpatient clinic visits*,* clinical testing and performed MRI scans of brain or spinal cord will be registered in the study as additional visits and scans*.

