#### Secondary analysis

The association between CSF profiles and the occurrence of any new spinal cord lesion within two years (binary outcome) will be evaluated using a multivariable logistic regression model with intrathecal IgM synthesis (standardized to z-scores using Reiber formula) as the primary predictor. Prespecified covariates are intrathecal IgG synthesis, presence of oligoclonal bands and kappa free light chains. Continuous predictors will be assessed for linearity in the logit and transformed or modelled with splines if needed, multicollinearity will be evaluated using variance inflation factors. Results will be reported as odds ratios with 95% CI. Model discrimination will be quantified by the area under the ROC curve. Distributions of lymphocyte subsets, soluble blood- and blood biomarkers, and clinical variables will be compared between groups with and without new SC-MRI activity, overall MRI activity, and NEDA status using independent *t*-tests or Mann–Whitney *U* tests for continuous variables and χ² tests for categorical variables. Exploratory analyses will compare other baseline characteristics (e.g., center of inclusion, disease duration, treatment choice) across lesion-based subgroups.

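### The 80% power stated for the CSF model holds only if CSF is available in about 95–100% of retained patients, because the target of 155 allows for loss to follow-up alone

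*Protocol article*

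**What the plan says.** The Sample size section sizes two analyses. The primary incidence estimate needs 139 patients. For the CSF logistic model, "an estimated sample size of 144 patients is needed to be able to detect an odds ratio of 2", "with a power of 80%, alpha of 0.05", where "the base expected proportion of patients with new cord lesions within two years is about 15" per cent and the "expected R-squared between main predictor variable and other covariates estimated 0.07 based on retrospective data". The 15% is set against two retrospective figures: 19% in a local database and 12% in an international registry of treatment-naïve patients starting a DMT. The target of 155 then follows from the calculated sizes and "an expected loss-to-follow-up of about 2–7% based on other longitudinal prospective MS MRI studies". The recruitment section confirms that loss to follow-up is what the sample size was corrected for, and that withdrawn subjects are not replaced.

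The Secondary analysis section specifies the model with "intrathecal IgM synthesis (standardized to z-scores using Reiber formula) as the primary predictor". It adds: "Prespecified covariates are intrathecal IgG synthesis, presence of oligoclonal bands and kappa free light chains".

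The Fig. 2 legend lists, among the baseline data, "cerebrospinal fluid data (if lumbar puncture took place as part of the diagnostic workup"). Table 2 does not make a lumbar puncture or available CSF a condition of entry. No section gives the expected share of patients with CSF.

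**The concern.** The 144 is a count of patients who can contribute to a model built wholly from CSF and intrathecal measures. The 155 is a count of enrolled patients, reduced only by loss to follow-up. The two are consistent only if nearly every retained patient has CSF, and the article makes CSF conditional without saying how often the condition will be met. By contrast, its MRI section states that all patients will have had a brain and spinal cord MRI before treatment.

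CSF is the one predictor selected a priori; the other factors are exploratory. The CSF model also sets the enrolment target: the primary estimate would need 139/0.93 = 149.5, so 150, while the CSF model needs 144/0.93 = 154.8, so 155. If many patients lack CSF, a null result for intrathecal IgM would be read against a power that the analysis did not have.

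**Working it through.** **Inputs.** From the Sample size section: odds ratio 2, event proportion 15%, R² 0.07, power 80%, alpha 0.05, N = 144, loss 2–7%, target 155. From the Secondary analysis section: the predictor is a z-score, so the odds ratio is taken as per standard deviation. Sidedness is not stated; two-sided is assumed. The share with CSF is not in the document; the values used below are assumptions.

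**1. Reproducing the 144.** The usual formula for one normal predictor is n = (1.960 + 0.842)² / [p(1−p)(ln OR)²(1−R²)]. With p = 0.15, OR = 2 and R² = 0.07 this gives 128.1/0.93 = 137.8. A Wald calculation with variance correction (Demidenko), taking 15% as the overall event rate, gives 146.1. Simulation of the Wald test at n = 144 (2,000 runs) gives power of 77.5% if 15% is the overall rate and 80.6% if it is the rate at the predictor mean. The figure of 144 is plausible and is taken as correct.

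**2. Reproducing the 155.** 144/(1 − 0.07) = 154.8, rounded up to 155.

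**3. Room left for missing CSF.**
- At 7% loss: 155 × 0.93 = 144.15 retained; 1 − 144/144.15 = 0.1% may lack CSF.
- At 2% loss: 155 × 0.98 = 151.9 retained; 1 − 144/151.9 = 5.2% may lack CSF.

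**4. Power by CSF share.** Evaluable n = 155 × (1 − loss) × share. Power is scaled to the plan's own claim, so that n = 144 gives 80%: power = Φ(2.802 × √(n/144) − 1.960). For example, at 90% coverage and 7% loss, n = 129.7 and power = Φ(2.802 × 0.949 − 1.960) = Φ(0.699) = 75.8%. The last column is 144/[(1 − loss) × share].

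| CSF share (assumed) | Evaluable n, 7% to 2% loss | Power, 7% to 2% loss | Enrolment that would keep 144, 2% to 7% loss |
|---|---|---|---|
| 100% | 144–152 | 80–82% | 147–155 |
| 95% | 137–144 | 78–80% | 155–163 |
| 90% | 130–137 | 76–78% | 164–173 |
| 80% | 115–122 | 71–73% | 184–194 |
| 70% | 101–106 | 65–67% | 210–222 |

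**5. Event range.** With all 144 evaluable, the formula in step 1, solved for power, is Φ(ln 2 × √(144 × p(1−p) × 0.93) − 1.960). It gives 74% at p = 0.12, 82% at 0.15 and 88% at 0.19. These values are unscaled: the formula needs only 137.8, so it gives slightly more than 80% at 144. They should not be mixed with the table.

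**The case against.** **The shortfall is conditional.** A reader might infer that the trial will miss its power. The documents do not support that, because the CSF share is unknown and at 95% coverage or more the loss is within about 2 points. By the simpler formula, which needs about 138, 80% power survives with CSF in 138/144.2 = 96% of retained patients at 7% loss and 138/151.9 = 91% at 2% loss. This stands, and it is why the result is given as a range. It does not rescue the statement as written, since the article neither requires nor asserts coverage that high.

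**The inputs are not shown to be favourable.** A reader might infer that 15% and R² 0.07 flatter the power, since the registry figure for treatment-naïve patients is 12%. But 15% lies between the plan's own 12% and 19%, and power moves in both directions (74% and 88%). Cord MRI in routine practice is mostly prompted by symptoms, whereas here every patient is scanned, so retrospective rates may be too low. The R² is attributed to retrospective data that are not shown, and nothing in the article supports a larger value. Neither input is faulted here.

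**Handling of missing covariates is not stated.** The article does not say that a patient lacking one assay is dropped, and that rule may sit in an analysis plan. This stands for a single missing assay. It helps little for a patient with no puncture, who has neither the main predictor nor any listed covariate; imputation would add little information on the IgM effect.

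**It is a secondary model in an observational study,** reported with confidence intervals that will show any imprecision. This limits the severity but does not correct the stated power.

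**Conclusion.** Wrong as written: the article states a power that its design does not secure. There is no arithmetic error, since 144 is plausible and 155 is the exact 7% inflation of it. What is missing is an allowance for patients without CSF in a model that consists only of CSF and intrathecal terms.

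The 80% holds if about 95% (at 2% loss) to 100% (at 7% loss) of retained patients have CSF. Below that, the shortfall is small at 90% coverage (76–78%) and material at 80% (71–73%) and 70% (65–67%). These figures rest on taking the plan's 144 as giving exactly 80%, on its 2–7% loss, on an assumed CSF share, and on patients without CSF contributing essentially nothing to the IgM estimate.

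The primary incidence estimate and its 139 do not depend on CSF. This is a should-fix.

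**What to change.** In the Sample size section, restate the power of the CSF model at the number of patients expected to have both follow-up and CSF. Inclusion was still open when the article was written, so CSF availability can be counted among the patients already included. Show the restated power over the plan's own event range of 12–19%, in a small table. Read a null result for intrathecal IgM against that restated figure. The prespecified covariates can stay as they are.

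The cost is a revised sentence and a table. No extra patients or procedures are needed. The downside is that the stated power is likely to look less favourable.

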### Statistical analysis

#### Primary analysis

The primary objective is to determine the incidence of new asymptomatic spinal cord lesions in the study population. The incidence of new asymptomatic spinal cord lesions will be calculated as the proportion of patients with at least one new lesion at the predefined follow-up timepoints. 95% confidence intervals (CI) will be calculated using exact binomial methods. The relationship between new asymptomatic spinal cord lesions and concurrent brain MRI activity will be assessed to identify lesions occurring independently of brain activity. From these data, the *number needed to scan* (NNS) will be calculated as the inverse of the proportion of patients with isolated asymptomatic spinal cord activity detected at 15 months (T2) and 27 months (T3) after DMT initiation.

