A commonly used outcome measure in MS drug trials is ’no evidence of disease activity’ (NEDA). NEDA-3 is defined as no relapses, no disability progression, and no new radiological activity on MRI. Regarding the latter, in almost every MS drug trial, only brain and not SC-MRI is included [16], with retrospective studies showing contrasting results regarding the value of adding SC-MRI in NEDA evaluation [6, 21]. However, inherent to the retrospective design of these studies, they suffer from selection bias. In a study investigating NEDA in a large cohort of MS patients using first- as well as second-line treatments, every year there were 8% − 12% more patients showing evidence of disease activity solely based on SC-MRI [20].

A recently introduced concept in MS is progression independent of relapse activity (PIRA) and/or progression independent of relapse and MRI activity (PIRMA), highlighting the significance of clinical disability progression that occurs regardless of relapse events or MRI findings. PIRA/PIRMA represents the proposed pathological mechanism of chronic neurodegeneration in MS as opposed to acute inflammation associated with relapse.

Evidence on the contribution of spinal cord lesions, particularly asymptomatic lesions, to PIRA/PIRMA remains scarce, largely due to the omission of routine spinal cord imaging in standard MRI protocols. Given that asymptomatic spinal cord lesions have been implicated in disability progression, insufficient monitoring of the spinal cord may lead to an underestimation of their potential role in the PIRA/PIRMA mechanism [4]. The operational definition of PIRMA may possibly require expansion to incorporate routine spinal cord MRI monitoring, thereby capturing asymptomatic spinal cord lesions that could otherwise confound assessments of progression independent of relapse and (brain) MRI activity.

We reported previously in a retrospective setting, that approximately a quarter of patients under a DMT developed new spinal cord lesions in the first 3 years after starting treatment (see Fig. 1) [11]. Other reports estimate that about 10–25% of spinal cord lesions are asymptomatic and therefore are missed when SC-MRI is not part of routine follow-up after starting a DMT [3, 22].

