Given that (asymptomatic) spinal cord lesions may occur with some frequency, possibly remain undetected in current follow-up regimens, and are not accounted for in the outcome measures of clinical drug trials—yet may have implications for future disability—an important question arises: should routine spinal cord follow-up be incorporated into standard clinical practice?

This study seeks to determine the frequency of asymptomatic spinal cord lesions in patients with early MS initiating their first disease-modifying treatment, and to evaluate whether spinal cord MRI detects disease activity not captured by clinical assessment or brain MRI alone.

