## Methods

### Aim of the trial

The primary objective of this study is to prospectively collect both full sagittal and axial SC-MRI data (in addition to routine brain MRI), in recently diagnosed MS patients, to address the following research questions:

What is the incidence of asymptomatic spinal cord lesions in patients commencing DMT? How frequently do asymptomatic spinal cord lesions occur in absence of radiological progression on brain imaging? In other words, how often is disease activity solely proven by SC-MRI and what is the number-needed-to-scan?

The secondary objective is to investigate which patients are predisposed to developing new spinal cord lesions during follow-up in early disease stages. Regarding this question, the primary focus will be on factors such as CSF profiles, lymphocyte composition in blood, blood biomarkers and clinical features.

We hypothesize that the detected incidence of asymptomatic cord lesions independent of brain MRI activity will be higher than the approximately 10% per year reported in retrospective studies [8, 20]. Additionally, we expect that more SC lesions occur in a subgroup of MS patients with CSF profile positive for intrathecal IgM, IgG synthesis and higher number of oligoclonal bands, a low number of transitional B cells at baseline, increased or decreased levels of sICPs at baseline, and/or a presenting clinical syndrome of optic neuritis or myelitis.

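### The number needed to scan leaves out patients with brain MRI activity but not those with a relapse elsewhere, so it can only equal or fall below the figure the aim asks for

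*Protocol article*

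**What the plan says.** The NNS is the "inverse of the proportion of patients with isolated asymptomatic spinal cord activity detected at 15 months (T2) and 27 months (T3) after DMT initiation" (Protocol article, Primary analysis). The sentence before it shows how activity comes to count as isolated: "The relationship between new asymptomatic spinal cord lesions and concurrent brain MRI activity will be assessed to identify lesions occurring independently of brain activity". The NNS is then computed from those data. No other comparator is named.

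The questions it should answer are set out earlier. Background and rationale says the study will "evaluate whether spinal cord MRI detects disease activity not captured by clinical assessment or brain MRI alone". Aim of the trial asks "How frequently do asymptomatic spinal cord lesions occur in absence of radiological progression on brain imaging" and then restates this as "how often is disease activity solely proven by SC-MRI and what is the number-needed-to-scan". Background and rationale also says what disease activity comprises: "NEDA-3 is defined as no relapses, no disability progression, and no new radiological activity on MRI".

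The clinical data are collected. "MS related relapses" are registered (Fig. 2 legend), and EDSS is scored at screening, T1, T2 and T3 (Clinical tests). NEDA status is used only in the Secondary analysis section, to group patients for marker comparisons. It plays no part in the NNS.

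**The concern.** Aim of the trial treats two quantities as one. The first is a silent cord lesion without brain MRI progression. The second is disease activity that only the cord scan shows. They differ whenever the patient had clinical activity from another site in the same interval. In the stated questions and in the NNS rule, the word asymptomatic is attached to the cord lesion or cord activity, so it does not by itself require that the patient was relapse-free.

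The NNS is the figure a reader would use to judge whether routine cord imaging earns its cost in scanner time and patient burden, which the article itself stresses. If its numerator includes patients whose disease activity was already known, the added yield is overstated and the NNS understated. A larger sample would not remove this, because it comes from the definition.

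**Working it through.** **The plan's own figure.** Inputs from the Sample size section: proportion 0.10, precision 0.05, confidence 95%.

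n = 1.96² × 0.10 × 0.90 / 0.05² = 138.3, rounded up to 139. This reproduces the stated 139. The section ties that proportion to absence of brain MRI activity, with no clinical condition. The article states no NNS; the planning rate implies 1/0.10 = 10.

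**Who is counted.** Take patients with a silent new cord lesion and a stable brain MRI, and vary the clinical course since the previous scan:

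| Clinical course | Counted as written | Activity shown only by the cord scan |
|---|---|---|
| No relapse, no EDSS worsening | yes | yes |
| Relapse from another site, e.g. optic neuritis | yes | no |
| Relapse from a second, symptomatic cord lesion | yes, if judged lesion by lesion | no |
| EDSS worsening without relapse | yes | contestable |

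**Direction.** Let p be the proportion counted as written and f the share of those patients who had a relapse in the interval. The intended proportion is p(1 − f), so the intended NNS is 1/[p(1 − f)]. Since f lies between 0 and 1, this is never below 1/p.

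**Size.** The documents give no f, so the values below are assumptions.

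- p = 0.10: f = 0 gives 10.0; f = 0.10 gives 1/0.09 = 11.1; f = 0.20 gives 1/0.08 = 12.5; f = 0.30 gives 1/0.07 = 14.3.
- p = 0.08 and p = 0.12 (the 8% to 12% per year cited in Background and rationale, used as alternative starting rates): f = 0 gives 12.5 and 8.3; f = 0.30 gives 17.9 and 11.9.

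**In patients.** With 144 evaluable (the larger of the two sample sizes before allowance for loss to follow-up) and exact binomial limits inverted to the NNS scale:

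- 14/144 = 9.7%: NNS 10.3 (95% CI 6.3 to 18.5).
- 11/144 = 7.6%, after removing 3 relapsing patients (3/14 = 21%): NNS 13.1 (95% CI 7.5 to 25.8).

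**Effect on the 139.** With n = 139, the half-width at p = 0.10 is 1.96 × √(0.10 × 0.90/139) = 0.050. At p = 0.07 it is 1.96 × √(0.07 × 0.93/139) = 0.042. A smaller proportion therefore still meets the stated absolute precision, although the interval for its inverse, the NNS, becomes wider.

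**The case against.** The best defence is that the terms are open. The rule counts patients, and the article defines neither isolated nor asymptomatic. Background and rationale speaks of new cord lesions arising without clinical signs or symptoms, which can be read at patient level and would then exclude relapses. A condensed article may leave such definitions to the full protocol. Aim of the trial also glosses its own phrase in terms of brain imaging, and nowhere is the NNS said to be based on NEDA. This lowers confidence but does not remove the point. The text does name a comparator, it is brain MRI alone, and the stated aim names clinical assessment as well.

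A second objection concerns disability. A reader might infer that every patient with EDSS worsening should also leave the numerator because the cord scan adds nothing there. The documents do not support that. Background and rationale argues that silent cord lesions may lie behind progression labelled as independent of relapse and MRI activity, so worsening with a new cord lesion is a case of interest. Visits are roughly yearly and T3 is the last, so worsening first seen at T3 cannot be confirmed at a later scheduled visit. Excluding unconfirmed fluctuation could push the NNS up wrongly. This objection stands, and it confines the main correction to relapses.

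Third, the overlap is assumed, and the two illustrated intervals overlap heavily. Both statements are true. They limit what can be said about size, not about direction.

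**Conclusion.** The point holds in a limited form. Followed as written, the NNS rule can count patients whose disease activity was already shown by a relapse at another site, so it does not match the aim of finding activity that only the cord scan reveals. The NNS can only be equal to the intended value or more favourable. At the 10% planning rate, assumed overlaps of 10% to 30% would raise it from 10 to between 11.1 and 14.3; with no overlap nothing changes.

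A reader might go further and conclude that the published NNS will certainly be biased, or that the primary result is compromised. Neither follows. The overlap may be zero, and a full protocol not shown here may define isolated activity at patient level. The primary incidence of asymptomatic cord lesions, its exact interval and the sample size of 139 do not depend on this definition. Severity is moderate.

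**What to change.** In Primary analysis, define the NNS numerator per scan interval as a patient with all three of the following since the previous scan:

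- a new asymptomatic cord lesion;
- no new brain MRI activity;
- no relapse of any localisation.

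Report the proportion conditioned on brain MRI alone, which the 139 was sized for, as a separate line. Add a sensitivity analysis in which the NNS also excludes EDSS worsening (NEDA-3 otherwise maintained), with the worsening threshold stated in advance and a note that worsening first seen at T3 cannot be confirmed at a later scheduled visit.

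The cost is wording and one extra line of output. Relapses and EDSS are already recorded, and the article reports that inclusion is still ongoing, so the rule can be fixed before results are known. The downside is that the headline NNS may become somewhat less favourable and less precise.
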